### **Treatments:**

Overall, 126 eligible participants will be randomly allocated to a 24-week group-based *yoga program* or *strengthening exercise program* (each with two 1-hour group-based sessions and one 1 hour home based session per week). Group sessions will be led by physiotherapist/exercise physiologists/yoga teachers for the first 12 weeks. Trainers will lead a group of approximately 10 participants. Participants will be instructed to continue their *yoga* or *strengthening exercise* at home for another 12 weeks. Using REDCap, weekly email follow-up will be done with the participants to confirm the compliance to the home-based program, and video instructions will be given to each participant to support the home-based program.

An evidence-based *yoga program* designed by a yoga expert and researcher - [name] from the Maryland University of Integrative Health, USA will be delivered by yoga

teachers. Each yoga class will begin with a breathing exercise (*pranayama*) and chanting (10min), warm-up, and moving sequences (*asanas*, 40 min). Classes will end with deep relaxation (*savasana*) and meditation (10 min). Classes will include an application of yoga philosophy and replace negative thoughts with positive ones (*pratipaksa bhavanam*). Details about interventions are in the appendix.

The strengthening exercise therapy regimen will be designed by [name] as a group-based progressive strengthening exercise program based on those used in past clinical trials and shown to be effective. Details about interventions are in the appendix.

### ***Safety:***

The participants will be asked to come to Menzies centre for the face-to-face group-based *yoga program* or *strengthening exercise program* wherever possible; however, in the event of participants not being unable to come to Menzies centre (due to COVID-19 related restrictions/lockdown) the *yoga program/strengthening exercise* classes will be run on zoom with the same teacher.

First 12 weeks of intervention in both groups will be via face-to-face classes and via zoom sessions if there is a lockdown due to Covid restrictions. The participants will be given a detailed information sheet on their yoga/ exercise sessions which they were doing in the first 12 weeks to continue in the next 12 weeks. We will give them short video of the individual sessions for reference.

Considering the COVID-19 situation, we have put the precautions below in place that will be observed during the trial.

1. The participants will enter the Menzies Institute for Medical Research facility after the routine temperature screening.
2. The group-based session will be performed in the rooms with designated COVID-19 capacity to accommodate the group of patients.
3. Patients will receive separate the yoga/exercise mat and elastic band that will not be shared with other participants.

Adverse events will be recorded throughout the study, and CIs will be notified of any serious events within 24 hours.

Adverse events will be monitored throughout the study. Yoga or exercise teachers and the unblinded research assistant will monitor AEs. Adverse events will be defined as any treatment-related problem that lasts for >2 days and/or caused the patient to seek other treatment. Potential AEs from this study include increased knee pain or pain at other sites, temporary muscle stiffness, falls or other injuries related to the exercise. There is a very rare chance of an exercise-induced heart attack or sudden death. AEs in our knee OA exercise trials have mostly been mild and transient and generally comprise of increased knee pain or pain at other sites, which has resolved by individualising the program to the participant's capabilities.

The teachers leading the yoga/strengthening exercise classes will ensure the exercises are performed safely. It is usual to feel some pain/discomfort in the knee during the exercise but the amount of pain will be monitored. When levels of pain are deemed unacceptable by the participant and/or teacher, the exercise program will be modified accordingly. Participants will use similar principles in the unsupervised home sessions. In particular, they will be advised that if the pain has not subsided to usual levels by the next day or there has been increased night pain or swelling in the knee, the exercise program should be modified by reducing the

intensity or frequency of the exercises or by leaving out one or more exercises that may be contributing to the increase in symptoms.

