### **Randomisation and blinding:**

Allocation of participants in a 1:1 ratio to either a 12-week *yoga program* or *strengthening exercise program* will be based on computer-generated random numbers prepared by a statistician with no involvement in the trial. Code-break for the full randomisation schedule will be maintained by the administering institute.

The assessors will be blinded to treatment allocation for objective outcome measures. Allocation concealment and blinding will be ensured by having two research nurses coordinate the trial. Assessments will be taken by the research nurse blinded to the group allocation.

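### An adverse event is counted only if it is treatment-related and either lasts over 2 days or prompts other treatment, with unblinded monitoring: harms are undercounted, and the arm comparison may be biased

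*Combined protocol and SAP*

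**What the plan says.** The definition is in the protocol's Safety section: "Adverse events will be defined as any treatment-related problem that lasts for >2 days and/or caused the patient to seek other treatment". The same section names the monitors: "Yoga or exercise teachers and the unblinded research assistant will monitor AEs". On serious events it says: "Adverse events will be recorded throughout the study, and CIs will be notified of any serious events within 24 hours". Serious is not defined.

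Among the potential events the section lists are "temporary muscle stiffness, falls or other injuries related to the exercise". It also says of earlier experience: "AEs in our knee OA exercise trials have mostly been mild and transient".

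Under Randomisation and blinding, the masking of assessors has a stated scope: "The assessors will be blinded to treatment allocation for objective outcome measures". Adverse events are not mentioned there. The schedule of assessments places adverse events at weeks 4, 8, 12, 16, 20 and 24. No section names who judges relatedness or gives criteria for it. Neither the protocol's outcome lists nor the SAP contains an adverse event outcome or a safety analysis.

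**The concern.** The usual order is to record what happened and then classify it. Here the classification comes first, and an event that fails it is not an adverse event at all. The filter has two parts, relatedness and a threshold of duration or care-seeking, and the people named to monitor know the allocation.

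The trial compares two active programmes, and the SAP's summary of changes (item 3) reports a move from superiority to non-inferiority on pain. If pain relief is judged similar, relative harms weigh more in choosing between the programmes. A count that rests on an unmasked, unspecified judgement is weak support for that choice, and some of what it omits is recorded nowhere else.

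**Working it through.** No figure in the plan bears on this point, so there is nothing to reproduce. The check is a reading of the definition, followed by an illustration of size.

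**Step 1: apply the definition to each kind of event.**

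| Event | Counted? |
|---|---|
| Related, over 2 days or other treatment sought | Yes |
| Related, 2 days or less, no other treatment sought | No |
| Non-serious, judged unrelated, any duration | No |
| Serious, judged unrelated | Unclear: the 24-hour notice states no relatedness condition, but the definition does |

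**Step 2: set the definition beside the rest of the section.** Falls and pain away from the knee are listed as potential events, yet one that settles within 2 days without other treatment fails the definition. Past events are described as mainly mild and transient, which is the class most exposed to a duration threshold. The section also says: "When levels of pain are deemed unacceptable by the participant and/or teacher, the exercise program will be modified accordingly". It does not say that such a modification is logged as an event. No view is taken here on the management rule itself; these parts of the section need to be reconciled with the definition.

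**Step 3: look for a safeguard elsewhere.** Assessor masking is limited to objective outcomes. There is no all-cause collection step, no masked attribution and no safety analysis.

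**Step 4: illustrate the size.** Inputs: 126 participants allocated 1:1, so 126/2 = 63 per arm (Sample size calculation; Randomisation and blinding), ignoring dropout. Assumed, not from the documents: a true proportion p with a problem, the same in both arms, and the share c of those problems that is counted.

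- Expected count per arm = 63 × p × c.
- Expected counted risk ratio = (p × c1)/(p × c2) = c1/c2.
- Chance of two-sided p<0.05, with q1 = p × c1, q2 = p × c2 and q̄ their mean: Φ((|q1 − q2| − 1.96 × SE0)/SE1), where SE0 = √(2q̄(1 − q̄)/63) and SE1 = √((q1(1 − q1) + q2(1 − q2))/63).

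*Equal capture, 50% in each arm, p = 40%.* True: 63 × 0.40 = 25.2 per arm. Counted: 63 × 0.40 × 0.50 = 12.6. Half the events are lost, but the expected ratio stays at 0.50/0.50 = 1.0.

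*Unequal capture, no true difference:*

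| Capture | Counted risk ratio | Chance of p<0.05 at p = 20% | 40% | 60% |
|---|---|---|---|---|
| 40% v 60% | 0.40/0.60 = 0.67 | 11% | 20% | 31% |
| 30% v 70% | 0.30/0.70 = 0.43 | 32% | 61% | 85% |

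With equal capture that chance is the nominal 5%. Loss of events thus needs only the definition; bias in the comparison needs capture or attribution to differ between arms.

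**The case against.** The strongest defence is that one rule applies to both arms. Collection is scheduled every 4 weeks in both, and the form is not shown, so participants may already be asked identical questions. Some knee discomfort during exercise is described as usual, so a threshold separating it from an event has a rationale. Knee-pain worsening is also captured without attribution by the VAS and WOMAC every 4 weeks, and medication changes are documented with reasons. All of this stands, and it narrows the loss. It does not cover falls or pain at other sites, and the health-service items concern knee pain.

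A reader might go further than the documents allow in four ways.

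- *That relatedness is judged separately in each arm by its own teachers.* The text says who monitors, not who decides. The research assistant is not tied to one arm. Teachers lead classes for only part of follow-up ("Group sessions will be led by physiotherapist/exercise physiologists/yoga teachers for the first 12 weeks"), while collection runs to week 24.
- *That unrelated events are never recorded.* The serious-event sentence carries no relatedness condition, so for serious events this is not established.
- *That temporary stiffness is always excluded.* Temporary is not defined as 2 days or less; stiffness that meets the definition counts.
- *That the comparison is biased.* There is a plausible route: the SAP's summary of changes (item 1) says one instructor took over 80% of yoga classes and another over 80% of strengthening classes, so personal reporting habits could align with arm. Nothing shows that they did, or in which direction.

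Finally, no comparison of harms is prespecified. That leaves a gap; it does not make a later comparison safe.

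**Conclusion.** The point holds in a limited form. Relative to all-cause, any-duration recording, the definition undercounts non-serious events judged unrelated and events of 2 days or less with no other treatment sought. This follows from the wording and needs no assumption about rates; the amount lost cannot be estimated from the documents. Differential bias is a possibility created by unmasked monitoring with no stated decision-maker. The risk ratios of 0.67 and 0.43 in the illustration rest wholly on assumed capture shares and show only what unequal capture would do. The status of unrelated serious events is an ambiguity to be resolved. The primary pain analysis is not affected; what is weakened is any statement about relative safety.

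**What to change.** At the contacts already scheduled for weeks 4 to 24, put the same standard, non-leading questions to every participant in both arms and record every untoward event regardless of cause or duration. Make relatedness, duration, seriousness and care sought separate fields. Define serious, and state that serious events are recorded whatever their cause. Reconcile the definition with the section's own list of potential events. In the SAP, prespecify by arm the number of events and of participants with at least one event, with all-cause as the main display and related events second.

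If relatedness is classified under masking, use narratives with references to the programme removed, and an existing team member who does not assess outcomes. A description of a posture or a band exercise could otherwise unblind the nurse who takes the objective measures. If masking is not feasible, label relatedness as an unblinded judgement; the all-cause counts do not depend on that attribution.

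The cost is a revised form and definition, somewhat more data entry, and more minor events in the report. No extra visits are needed.

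The SAP already describes the final manuscript, so collection may be complete. In that case, state the relatedness and duration filter and the unblinded ascertainment beside any comparison of adverse events, and draw no firm conclusion on relative safety.

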**Analgesic use:**

To maintain the pragmatic nature of the study, there will be no constraints with regard to the use of analgesic medications. All participants will be allowed to continue taking the medications that they are taking at their screening visit for the duration of the trial. Participants will be asked to keep medications as stable as possible, but if a participant requires an increase in analgesics this will be permitted, and the reason for the dose increase and the dose used will be documented.

**Outcomes and assessments:**

There will be four study clinic visits (screening, baseline/week 0, week 12, week 24) for objective assessments such as core physical function measures, muscle strength, neuromuscular variables, and functional balance. Pain and function will be assessed at each time point (week 0, 4, 8, 12, 16, 20, and 24) using a 100mm visual analogue scale (VAS) and asked: “On this line, how would you rate your symptoms in the last week”? We will also assess symptoms using the WOMAC scale. We will include other questionnaires on psychological, QoL (AQoL and EQ-5D), as well as adherence to therapy and healthcare utilisation of the treatment for knee OA.

**Primary outcome:**

Change in knee pain assessed by VAS for over 12 weeks. Pain will be evaluated at each time point using a 100mm VAS and asked: “On this line, how would you rate your overall average knee pain in the last one week”? For knee pain assessed using VAS, terminal descriptors will be 0mm = no pain, 100mm = worst pain possible.

**Secondary outcomes:** (overall change from baseline to week 12 and overall change from baseline to week 24 are separate outcomes)

1. Change in VAS knee pain over 12 weeks in patients with painDETECT>12
2. Change in VAS knee pain over 24 weeks.
3. Change in WOMAC knee pain, WOMAC stiffness, and WOMAC knee function over 12 weeks and over 24 weeks.
4. Change in physical function as assessed by 30s Chair Stand Test, 40m Fast Walk Test and Stair Climb Test over 12 and over 24 weeks
5. OMERACT\_OARSI responders (meeting responder criteria) at week 12, and 24 weeks
6. Change in biomarker (urinary CTX-II, serum COMP, and serum hyaluronan) and systemic inflammatory markers (hs-CRP, IL-6, TNF- $\alpha$ ) over 12, and over 24 weeks
7. Change in Patient Health Questionnaire (PHQ-9) scales over 12, and over 24 weeks
8. Change in patient global satisfaction score over 12, and over 24 weeks
9. Change in painDETECT scores over 12, and over 24 weeks
10. Change in leg muscle strength (quadriceps) over 12, and over 24 weeks
11. Change in gait speed from baseline to week 12 and baseline to 24 weeks

**Health Economics Outcomes (secondary outcomes):**

We will assess health state utility (HSU) values, resource utilisation, and costs throughout the study. Health-related quality of life (HRQoL) and utility will be assessed using the Assessment of Quality of Life (AQoL-8D) and the EuroQol 5 dimensions (EQ-5D-5L) instruments. The health economic outcomes to be collected as the secondary outcome will include:

12. Change in concomitant medications (assessed using self-reported medication history questionnaire) from baseline to 12 and baseline to 24 weeks and associated costs.

13. Self-reported adherence to the intervention and comparator program from baseline to 12 and baseline to 24 weeks assessed using online logbook and defined as the percentage of prescribed session undertaken.
14. Change in QoL (assessed by AQoL-8D and EQ-5D-5L) from baseline to week 12 and baseline to 24 weeks.
15. Change in health resource utilisation (assessed using a self-reported questionnaire) at 12 and 24 weeks.

#### **Other outcomes:**

16. Change in gait characteristics such as step length, double support time, step width, and step time from baseline to week 12 and baseline to 24 weeks.
17. Change in body fat will be assessed using bioelectrical impedance analysis (BIA) (BIA analyser, Quantum II, RJL Systems, Michigan, USA) at baseline, week 12, week 24. We will assess fat-free mass, percentage fat-free mass, fat mass and percentage fat mass.

The health economic measures to be collected at baseline, 12-week, and week 24 include: health service use including visits to GPs, specialist doctors, physiotherapists; medical imaging, procedures, tests and investigations for knee pain; hospital admissions and attendances for knee pain, and community service use for knee pain. We will also collect information on costs for transport and specialised equipment purchased/hired due to knee pain. We will collect information about employment, days absent from work, presenteeism, and sick leave due to knee pain. To assist with cost estimation, we will collect information about participants' concession, health care card & private health insurance status.

In combination with the clinical data, these data will be used to conduct a cost-effectiveness analysis of *yoga program* versus *strengthening exercise program*. We will test that hypothesis that *yoga program* will be cost-effective than the *strengthening exercise program*.

#### **Demographics and Medicare Number**

At the screening, we will collect information on sex and date of birth. At baseline, we will record participants' Medicare numbers for future data linkage.

**The OARSI-OMERACT responder criteria:** will be employed to generate a responder categorical variable (0 = non-responder, 1 = responder) based on improvement in WOMAC pain, function, and patient's global assessment. Patients' global assessment was evaluated using a 100 mm VAS.

**Core physical function measures:** including 30-second chair stand test, 40m (10m × 4) fast-paced walk test and stair climb test, will be performed as recommended by the OARSI guidelines for clinical trials at baseline and week 12 using the same equipment and at the same location. The total number of chair stand in 30 seconds, time to complete 40 m walk with three turns and time to ascend and descend a 9-step stair (20cm step height and handrail) will be recorded.

#### **PHQ-9:**

Depression may be an effect modifier. It will be assessed using the Patient Health Questionnaire (PHQ-9) at weeks 0, 12, and 24. The PHQ-9 is a validated tool for screening, diagnosing, monitoring, and measuring the severity of depression. It consists of nine questions, based on the Diagnostic and Statistical Manual of mental disorders (DSM-IV) criteria for the diagnosis of major depressive disorders in patients with medical illnesses.

*Procedure regarding the identification and management of moderate to severe depressive symptoms in the PHQ-9 scale:*

A score of 15 or more (out of 27) on the PHQ-9 is provisionally diagnostic of moderate to severe major depression. Furthermore, question 9 assesses suicide ideation. Any positive response (i.e. “several days”, “more than half the days”, or “nearly every day”) warrants immediate management.

As part of a duty of care, PHQ-9 scores will be assessed immediately by a member of the research team at the study visit [baseline, 12 weeks (3 months), 24 weeks (6 months)]. It will be screened for scores of 15 or more, or any positive response to question 9. Any participants with scores 15 or more or with positive responses for suicide ideation will be encouraged to contact their GP. We will also provide these participants with phone numbers for support services, including Lifeline and Beyond Blue. Any positive responses and actions taken will be logged and maintained on a study register.

### **Gait characteristics**

Gait will be assessed using the footfalls recorded on the GAITRite system, a 4.6 m computerized walkway. Measures gait characteristics such as gait speed (cm/s), step length (cm), double support time (ms), step width (cm), and step time (ms) will be directly obtained from the GAITRite software.

### **Physical activity (using accelerometers)**

We will ask the participants to wear accelerometers for a week before the start of intervention, 12 weeks and 24 weeks. We will assess the change in objectively measured physical activity between the groups.

### **Change in medication use**

All participants will be asked to continue therapy with the medications they were receiving at their screening visit for the duration of the trial. They will also be asked to keep their medication use as stable as possible; any medication changes were documented with the reason, drug name, and dose and were classified as commenced or increased, discontinued or decreased, or stable use or nonuse. A rescue medication, paracetamol, will be provided if the participant requested it. Medication use will be recorded at baseline and each follow-up period.

### **Data integrity and management**

We will collect all data using REDCap, a secure web application for managing databases. Paper copies of participant questionnaires will be stored in locked filing cabinets, with restricted access. Electronic data will be kept on password-protected servers, separating the identifying and non-identifying information. The codes linking data to identifying participant information will be kept separately from the study data, under password protection, and with restricted access. Only members of the study team who need to contact trial participants, enter data, or perform data quality control will have access to identifiable information. Daily backups of all electronic data will occur to minimize any risk of lost data.

Blood results will be identifiable. Only our research staff and pathology staff will have access to these, and they will be stored in the same manner as outlined above.

After the completion of trial, paper copies of data will be archived in secure storage. Any identifiers will not be removed, in case of follow-up of study participants being necessary, but the electronic data will continue to be maintained in a secure electronic database, separating identifying and non-identifying information. This will remain password-protected and with access given only to the investigators unless otherwise authorized by the investigators.

| Items/Variables                                                                                                                                                                                                                                                                                                                                                      | Screening | Baseline
(week 0) | Week 4 | Week 8 | Week 12 | Week 16 | Week 20 | Week 24 |
|----------------------------------------------------------------------------------------------------------------------------------------------------------------------------------------------------------------------------------------------------------------------------------------------------------------------------------------------------------------------|-----------|----------------------|--------|--------|---------|---------|---------|---------|
| Informed consent                                                                                                                                                                                                                                                                                                                                                     | x         |                      |        |        |         |         |         |         |
| Randomisation                                                                                                                                                                                                                                                                                                                                                        |           | x                    |        |        |         |         |         |         |
| Safety for exercise clearance                                                                                                                                                                                                                                                                                                                                        | x         |                      |        |        |         |         |         |         |
| ACR clinical criteria for knee OA                                                                                                                                                                                                                                                                                                                                    | x         |                      |        |        |         |         |         |         |
| Medicare number                                                                                                                                                                                                                                                                                                                                                      |           | x                    |        |        |         |         |         |         |
| Clinical measures                                                                                                                                                                                                                                                                                                                                             |           |                      |        |        |         |         |         |         |
| Bloods (stored for cartilage/ synovium/
inflammatory markers)                                                                                                                                                                                                                                                                                                     |           | x                    |        |        | x       |         |         | x       |
| Core physical function tests                                                                                                                                                                                                                                                                                                                                         |           | x                    |        |        | x       |         |         | x       |
| Leg muscle strength test                                                                                                                                                                                                                                                                                                                                             |           | x                    |        |        | x       |         |         | x       |
| Height and weight                                                                                                                                                                                                                                                                                                                                                    |           | x                    |        |        | x       |         |         | x       |
| Gait characteristics                                                                                                                                                                                                                                                                                                                                                 |           | x                    |        |        | x       |         |         | x       |
| Body composition (using BIA)                                                                                                                                                                                                                                                                                                                                         |           | x                    |        |        | x       |         |         | x       |
| Physical activity (using accelerometers)                                                                                                                                                                                                                                                                                                                             |           | x                    |        |        |         |         |         | x       |
| Questionnaires                                                                                                                                                                                                                                                                                                                                                |           |                      |        |        |         |         |         |         |
| Knee pain VAS                                                                                                                                                                                                                                                                                                                                                        | x         | x                    | x      | x      | x       | x       | x       | x       |
| Knee WOMAC                                                                                                                                                                                                                                                                                                                                                           |           | x                    | x      | x      | x       | x       | x       | x       |
| PainDETECT                                                                                                                                                                                                                                                                                                                                                           |           | x                    |        |        | x       |         |         | x       |
| PHQ-9                                                                                                                                                                                                                                                                                                                                                                |           | x                    |        |        | x       |         |         | x       |
| Patient global evaluation                                                                                                                                                                                                                                                                                                                                            |           | x                    | x      | x      | x       | x       | x       | x       |
| Health Economics Outcomes:
Medication cost diary
Health service utilization (visit to GP,
practice nurses, and any other health
professionals (e.g. physiotherapists))
Employment/Days off work
Concession/Health Care Card
Private Health Insurance
Transport & Specialised Equipment Costs |           | x                    |        |        | x       |         |         | x       |

|                                       |  |             |   |   |   |   |   |   |
|---------------------------------------|--|-------------|---|---|---|---|---|---|
| Safety (AEs)                          |  |             | X | X | X | X | X | X |
| EQ-5D and AQoL-8D                     |  | X           |   |   | X |   |   | X |
| Consent to contact for future studies |  |             |   |   |   |   |   | X |
| Early withdrawal information          |  | As required |   |   |   |   |   |   |

